## Abstract

**Background:**

Involuntary treatment refers to care where persons living with dementia are excluded from decision-making or do not provide consent. Despite serious consequences, involuntary treatment is often used in people with dementia receiving homecare. To address this, the Prevention and Reduction of Involuntary Treatment at Home (PRITAH) intervention was developed. A previous study indicated potential for scaling up PRITAH in professional homecare settings. However, implementing healthcare interventions like PRITAH is complex and often faces challenges. The current protocol describes a study that aims to: (1) gain a comprehensive understanding of the PRITAH- implementation in professional homecare settings, and (2) evaluate its effect on involuntary treatment use on people living with dementia at home.

**Methods:**

This quasi-experimental Hybrid Design Type-3 effectiveness-implementation study includes 88 case managers in the field of dementia care (CMDs) from four professional homecare organizations in Southern Limburg, the Netherlands. CMDs are divided into an intervention and control group stratified by geographical location. The intervention group receives the PRITAH-intervention, while the control group continues usual care. Data collection occurs at baseline (T0), 8 weeks (T1), and 20 weeks (T2) using questionnaires with open-ended and closed (Likert-scale) questions. Primary implementation outcomes include adoption, acceptability, appropriateness, feasibility, fidelity, and sustainability. Additionally, qualitative data from focus groups will be analysed. The primary effectiveness outcome is involuntary treatment use in people living with dementia at home, assessed via self-administered questionnaires completed by CMDs regarding ten randomly assigned clients within their caseload. Outcomes on CMD level include attitude, subjective norms, perceived behavioural control, and intention, which are prerequisites for behavioural change. Both descriptive analysis (quantitative) and content analysis (qualitative) evaluate implementation outcomes, while mixed (multilevel) linear regression models assess the effect of the PRITAH-intervention on involuntary treatment use.

**Discussion:**

This study provides insight into both implementation and effectiveness of the PRITAH-intervention in professional homecare settings. Due to potential contamination from communication among CMDs within the same organization and region, strict randomization is not feasible. Instead, a quasi-experimental design ensures a controlled comparison while maintaining real-world applicability. Including all available CMDs in the region enhances study’s validity, strengthening the intervention’s potential for broader implementation.

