#### Sample

The study will take place within the region of South Limburg in the Netherlands, home to a population of 402,700 individuals [38]. Of this population, 27.4% are 65 years or older and 2.2% (8,660 individuals) are diagnosed with dementia [39, 40]. In 2020, CMDs supported approximately 33–41% (i.e. 2,858 to 3,551) of the people living with dementia at home in the region [41]. In this large region, 88 CMDs employed by four professional homecare organizations are responsible for the dementia care in this region. Each CMD manages a caseload of approximately 55 clients (i.e. PLWD) in a fulltime position or proportionally in a part time position. All 88 CMDs working in the region of South Limburg in the Netherlands are invited to participate in the study on the implementation of the PRITAH-intervention. The CMDs are employed across four organizations in two regions and are each assigned to a specific city district or village within that region. To avoid contamination, all CMDs within the same district or village are grouped together, resulting in multiple clusters. These clusters are then allocated to either the intervention or the control condition, ensuring that CMDs within a given cluster did not interact across conditions. The CMDs in the intervention group receive training in batches of 10 to 14 people, with a two-week delay between the start of each batch’s training. CMDs in the control group will provide care as usual, continuing their routine work. They will not receive any PRITAH components (policy, kick-off meeting and training, on-the-job coaching and consultation, and alternatives for involuntary treatment). Moreover, CMDs in the control group are free to address involuntary treatment according to their usual practice in their respective organization. CMDs on maternity leave, long-term sick leave, nearing retirement, or newly recruited during the PRITAH-implementation period are excluded from the study. In a nested design, as part of the effect study, all 88 participating CMDs will report on the use of involuntary treatment by formal and informal caregivers for 10 randomly selected clients within their caseload to provide insights at the client level. If a client drops out of the study due to discontinuation of care (i.e. institutionalization or end of life), they will be replaced by another randomly assigned client from the caseload of the CMD. Therefore, we anticipate collecting 880 responses on client level. See Fig. 1.

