##### Effect outcomes

Outcomes at the CMD level (attitude, subjective norms, perceived behavioural control, and intention) will be analysed with mixed (multilevel) regression, with linear regression for continuous outcomes and generalized linear regression (e.g., logistic, ordinal, gamma) for categorical outcomes. A total score per CMD or client per time point will be calculated for each outcome measure if multiple items measure the same construct and share the same response format (e.g. all items are binary or all items use a 5-point Likert scale). Repeated outcome measures are nested within CMDs. The fixed (predictor) part of the mixed model will include intervention (yes/no), region, care organization, and time point (t0, t1, t2; week 0/8/20), along with age, gender, educational level, work experience in care for older people, work experience in professional home care, current position, number of working hours, and hours working with individuals with dementia. Additionally, interaction of each predictor with time will be evaluated. The random part of the model will account for unexplained outcome variation between CMDs, which is allowed to change over time, by assuming an unstructured residual covariance matrix (marginal model). Predictor by time interactions will be deleted if not significant, with exception of the key interaction between intervention and time. Giving the nonrandomized treatment assignment, additional analysis will be (a) comparing treated and controls with respect to the baseline outcome measurement, adjusted for all abovementioned confounders, and (b) repeating the above mixed regression, but now with the baseline outcome as covariate instead of as repeated measures. This approach will help assess Lord’s paradox as a sensitivity/robustness analysis [43, 55].

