## Discussion

The current protocol describes the design of a quasi-experimental Hybrid Design Type-3 effectiveness-implementation study. Implementing new healthcare interventions into real-world practices can be challenging and time consuming [57]. Challenges regarding implementation often depends on the context in which the intervention is implemented, the individuals in the process, and the characteristics of the intervention itself [58, 59]. To address these challenges, conducting a context analysis is essential [58, 60]. Therefore, the current protocol was developed based on the results from a prior context analysis for the PRITAH-implementation (*to be submitted*). In two focus groups with policy staff members, a district nurse, CMDs, managers, and directors, we explored barriers and facilitators using the Consolidated Framework for Implementation Research (CFIR) [58, 60]. Overall, the context analysis revealed that both participating home care organizations support the implementation of PRITAH to prevent or reduce involuntary treatment at home.

Although randomized controlled trials (RCTs) are considered the gold standard in research, our study uses a quasi-experimental design. This type of design is more often recognized for their use in implementation studies where strict randomization may be infeasible or unfitting [61]. In our study, communication between CMDs within the same care organisation and region might induce treatment contamination. Hence, stratification based on region and district is necessary.

A Hybrid Type 3 Design is well suited for this study as the success of the PRITAH-intervention is determined both by how well it can be implemented into existing homecare settings and by its effect on client outcomes. Recommended conditions for a Type 3 Design, as outlined by Curran and colleagues, further support his approach The first condition is that, although the full effectiveness of the PRITAH intervention has yet to be established, research has demonstrated sufficient indirect evidence of its effectiveness, warranting further exploration of its implementation. Another supportive condition for this type of design is the legislation on involuntary treatment (Care and Coercion Act) and the in 2024 released guidelines, which creates a good momentum for implementation [35, 62].

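### Contamination argues against randomising individual case managers, not the district or village clusters that the plan already allocates whole

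*Protocol article*

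**What the plan says.** The reason against randomising appears twice. The Abstract (Discussion paragraph) states: "Due to potential contamination from communication among CMDs within the same organization and region, strict randomization is not feasible". The main Discussion section states: "communication between CMDs within the same care organisation and region might induce treatment contamination. Hence, stratification based on region and district is necessary". Beside this stands a general remark that quasi-experimental designs suit "implementation studies where strict randomization may be infeasible or unfitting", and the Abstract mentions real-world applicability. Neither names a further obstacle specific to this study.

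The Sample section (under Study setting and sample) describes how contamination is handled: "To avoid contamination, all CMDs within the same district or village are grouped together, resulting in multiple clusters". It continues: "These clusters are then allocated to either the intervention or the control condition, ensuring that CMDs within a given cluster did not interact across conditions". Neither the number of clusters nor the rule that assigns them is given.

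The Effect outcomes part of Data analyses confirms that assignment is not random and responds to it: "Giving the nonrandomized treatment assignment, additional analysis will be (a) comparing treated and controls with respect to the baseline outcome measurement". It also plans adjustment for CMD and client characteristics, region and care organization, and a repeat of the model with the baseline outcome as covariate.

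**The concern.** The article draws a conclusion that its own Sample section does not support. Contamination is a sound reason not to randomise CMDs one by one, because colleagues in one district would fall into different arms. The remedy is to allocate groups, and the plan does so. Once whole groups are allocated, the protection within a group comes from the grouping. It is the same whether the groups are assigned by lot or by choice.

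What is at stake is the effectiveness aim. If someone chooses which districts receive the intervention, the choice may follow enthusiasm, staffing, management support or convenience. Such features can also influence how involuntary treatment, or its reporting, changes over 20 weeks. Randomising the clusters would remove deliberate selection. The implementation outcomes are descriptive and rest mainly on intervention-group CMDs, trainers and managers, so this point does not affect them.

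**Working it through.** The article states no power, alpha, effect size, SD, intracluster correlation (ICC) or number of clusters, so there is no figure of its own to reproduce on this point. The check is mainly one of logic.

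**1. Reason against remedy.**
- Abstract and Discussion: CMDs in one organization and region communicate, so randomisation is infeasible.
- Sample: CMDs in one district or village are kept together, and the cluster is the unit of allocation.
- Consequence: the reason applies to the CMD as unit. The plan does not use that unit.

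**2. Does wider communication restore the reason?** The stated worry covers organization and region, which are larger than a district or village. The planned model contains intervention, region and care organization together. If every organization were wholly in one arm, intervention could not be separated from organization; the same holds for region. The model therefore presupposes both arms within at least one organization and within at least one region. The Abstract's stratification by geographical location points the same way. Communication between clusters thus appears possible under the present allocation too. Non-random assignment would limit it only if neighbouring districts were deliberately kept in one arm, and the article does not say so.

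**3. What the planned analyses can correct.** The key term is intervention by time, so stable level differences between arms largely cancel. Differences in trend do not. The CMD covariates are personal and job characteristics. None describes a district's motivation, staffing or management support, and perceived workload is collected but is not in the model list. According to Measurements, T0 follows the kick-off meeting, which controls do not receive (Sample). The baseline used to examine selection is therefore taken after allocation and after first exposure.

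**4. Does randomising the same clusters cost precision?** Assumed: 44 v 44 CMDs, 8 to 24 clusters of equal size m = 88/K, ICC 0 to 0.10, 80% power, two-sided 5%.
- Design effect: DE = 1 + (m − 1) × ICC. With K = 8, m = 11 and ICC 0.10, DE = 1 + 10 × 0.10 = 2.0.
- Minimum detectable difference: (1.96 + 0.84) × √(DE × 2/44), which is 0.60 SD at DE 1 and 0.84 SD at DE 2.

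The method of assignment does not enter the formula. Sample size and design effect are the same either way.

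**5. Illustration of the stakes, with assumed inputs only.** Let b be the between-arm difference, in SD, that remains after adjustment and is not caused by the intervention. With SE = √(DE × 2/44), the actual error of a nominal 5% test is 1 − Φ(1.96 − b/SE) + Φ(−1.96 − b/SE).

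| b (SD) | DE 1 | DE 1.5 |
|---|---|---|
| 0 | 5.0% | 5.0% |
| 0.1 | 7.6% | 6.7% |
| 0.2 | 15.5% | 11.9% |
| 0.3 | 29.1% | 21.0% |

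Nothing in the article says which row applies, and b = 0 is possible.

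**The case against.** The strongest reply is that the clusters are not proof against contamination. The Sample section vouches only for CMDs within a cluster, the policy element is introduced through each organization's management, and a random draw could scatter the arms across neighbouring districts where a deliberate allocation might keep them apart. This stands in part. A reader might infer that randomising would give identical protection and that the plan gives up randomisation for nothing. The article does not support that: practical reasons may exist, and with few clusters chance imbalance would remain. But no such reason or deliberate grouping is stated, and the wider path appears open already.

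A second reply is that the design is openly quasi-experimental, with concurrent controls, a baseline, covariate adjustment and a sensitivity analysis. That is true. It would be wrong to say that the comparison rests on model adjustment alone, or that motivated districts were in fact selected. What remains is bias from unmeasured differences in trend.

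A reader might also see a contradiction in "Hence, stratification based on region and district is necessary", since stratifying by district would split a district across arms. The Sample section makes the unit plain and the sentence follows from the contamination argument, so this is loose wording.

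Finally, an article may leave the assignment procedure to a fuller protocol. The point does not rest on that gap. It rests on a stated inference that the article's own design undercuts.

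**Conclusion.** The point holds in a limited form. The only study-specific reason given for non-random assignment does not apply to the unit that the plan allocates. The cost is exposure of the effect comparison to unmeasured differences between districts, which the planned analyses can lessen but not remove. The size of any bias cannot be derived from the article. The error rates under working depend on an assumed residual imbalance and assumed equal arms, and show sensitivity only. The conclusion that randomising the same clusters needs no extra participants does not depend on those values.

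**What to change.** **If allocation is still open.** Assign the existing clusters by a computer-generated list, stratified by region and, where cluster numbers allow, by care organization. Take T0 before the kick-off meeting and before allocation is disclosed, and describe the design as cluster-randomised. The cost is some scheduling work for the training groups and a resequencing of T0 and the kick-off. Chance imbalance is possible if clusters are few. Communication between neighbouring districts would remain, and could be limited by merging adjacent districts into one cluster, at the price of fewer clusters.

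**If allocation is done**, as the past tense in the Sample section may suggest. Remove contamination as the reason that randomisation was infeasible, state how and why clusters were assigned, and word the effect conclusion as non-randomised evidence. This costs only text.

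**In either case.** Reword the Discussion so that region is the stratum and the district or village is the unit of allocation.

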## Background

People living with dementia (PLWD) suffer from severe impairments in memory, reasoning, language, and ability to perform everyday tasks [1]. Despite progressive cognitive decline, most (70%) people living with dementia (PLWD) wish to continue living in their own home environment for as long as possible [2]. Many countries support this preference through aging-in-place policies [3–6]. Aging in place fosters independence and autonomy and encourages PLWD to rely on family and friends for support [7–9]. However, caring for PLWD can be demanding due to complex needs and many PLWD requires extensive family, social, and professional support [9–12]. As dementia progresses, the caregiving role may place significant physical, emotional, psychological, and financial burdens [10, 13, 14]. Additionally, since PLWD lose decision-making capacity, caregivers often make decisions on their behalf. This may lead to ethical dilemmas between ensuring safety and respecting personal freedom [15, 16]. When the PLWD is not involved in the decision-making process, does not consent to their care, or resist care provided by professional and informal caregivers, it is referred to as involuntary treatment [17, 18]. Involuntary treatment includes (a) non-consensual care, which is defined as “any type of care that limits the organization of a person’s own life”, such as forced ingestion of food or fluids and enforced personal hygiene [17, 19]; (b) physical restraints defined as “any action or procedure that restricts a person’s free body movement to a position of choice and/or prevents normal access to his/her body by any method attached or adjacent to a person’s body that he/she cannot control or remove easily [20]”; and (c) the use of psychotropic medication without consent, including off-label prescriptions (i.e. prescribing a drug outside its licensed indication or medication prescribed for an unapproved indication, such as managing challenging behaviour and dementia-related symptoms) [21].

Involuntary treatment negatively affects PLWD and their (informal) caregivers, increasing aggression, agitation, and injury risks. In turn, these consequences significantly diminish the overall physical and psychological well-being [22–24]. Despite these adverse effects, research indicates that involuntary treatment is still commonly used. In the Netherlands and Belgium, over half of the PLWD receiving professional homecare experience some type of involuntary treatment, with non-consensual care being the most common [17]. Involuntary treatment is used by informal caregivers in 73.6% of the cases, by nurses in 57.9% of the cases, and by general practitioners in 13.6% of the cases [25]. Caregivers often view involuntary treatment as a necessary component of their care, especially when safety or well-being is at risk. For instance, locking the front door to prevent a person with dementia from wandering outside. However, this mindset contributes to the continued use of involuntary treatment [18].

To reduce involuntary treatment use, the Netherlands has implemented legislation, called the Care and Coercion Act, which mandates that involuntary treatment should only be applied as an *ultimum remedium* (i.e. last resort) after exploring alternatives. The law requires long-term care organizations to revise policies on involuntary treatment and monitor the results [26]. In response, the Dutch Association of Nurses and Caregivers (V&VN) developed a practical guideline to help healthcare organizations comply with the law, which was published in 2024 [27]. Despite these regulatory efforts, the high prevalence of involuntary treatment in PLWD at home highlights the need to support caregivers in reducing involuntary treatment.

The Living Lab in Aging and Long-Term Care Limburg (Maastricht University) developed the intervention ‘Prevention and Reduction of Involuntary Treatment At Home (PRITAH)’ in 2018. PRITAH aims to support both formal and informal caregivers with knowledge and tools for preventing and reducing involuntary treatment use at home [28]. The PRITAH-intervention was based on the effective EXBELT intervention, which was designed to prevent and reduce physical restraint in nursing homes [29, 30]. A previously conducted exploratory mixed-methods study tested PRITAH’s feasibility in professional homecare organizations, showing potential for implementation after minor modifications. The study evaluated PRITAH at two time points, showing a positive impact on healthcare professionals’ subjective norms (T0 = 3.1 vs. T1 = 3.5 on a 5-point Likert scale) and perceived behavioural control (T0 = 3.6 vs. T1 = 3.9 on a 5-point Likert scale), which are prerequisites for behavioural change for preventing and reducing involuntary treatment use [28, 31]. These findings provide promising expectations for upscaling the PRITAH- intervention in professional homecare settings to reduce involuntary treatment use.

Implementing and upscaling healthcare interventions like PRITAH on a large scale is complex and often hindered with barriers that delay the implementation [32–34]. To address these challenges and ensure that evidence-based interventions like PRITAH reach their full potential, such as preserving the freedom and autonomy of PLWD, it is essential to gain more understanding of the implementation. However, focusing solely on implementation is insufficient, as the intervention’s effectiveness must also be ensured. By adopting a dual focus on both implementation and effectiveness, research can increase the likelihood of successful implementation, streamline the process, and save valuable time. Curran and colleagues introduced hybrid effectiveness-implementation designs to address both the effectiveness of an intervention and its practical implementation [35].

The current study focusses on the implementation of the PRITAH-intervention. Hence, the current study protocol describes a Hybrid Type 3 effectiveness-implementation study, as outlined by Curran et al. [35]. The aim of this paper is to provide a detailed protocol of our Hybrid Type-3 effectiveness-implementation study to (1) gain a comprehensive understanding of the PRITAH- implementation outcomes in professional homecare settings, and (2) evaluate its effect on involuntary treatment use on PLWD at home.

